### Secondary objectives

To compare:The risk of severe illness from 48 h after randomization until 14 weeks of life among HIV-1-exposed infants administered BCG at birth with those receiving delayed BCGHIV-1-exposed infants who received BCG at birth with those administered a delayed BCG with respect to the occurrence of diarrhea, pneumonia and/or severe illness from 14 weeks to 1 year of ageHIV-1-exposed infants who received BCG at birth with those administered a delayed BCG with respect to the occurrence of severe illness during infancyOccurrence of diarrhea, pneumonia and/or severe illness during infancy in HIV-1-exposed infants vaccinated with BCG at birth versus those who receive delayed BCGThe mortality from birth to 14 weeks of age in HIV-1-exposed infants vaccinated with BCG at birth versus in those who are yet to receive BCGInfant mortality between HIV-1-exposed babies vaccinated with BCG at birth versus in those who receive delayed BCGThrough life-cycle modeling, long-term aggregate health benefits and cost-implications of the delivery strategies, and estimate their cost-effectiveness

To increase the diagnostic specificity, we will also try to capture “clinical sepsis^2^,” where an infant with severe illness and a negative blood culture, or from whom a blood culture could not be taken, has two or more of the following findings: total lymphocyte count (TLC) <5000 cells/mm^3^, absolute neutrophil count <1,500 cells/mm^3^, band to total polymorph ratio >0.2 and both of two C-reactive protein (CRP) levels >1 mg/dl in two specimens taken 24 to 48 h apart. Because we are yet to know in what proportion we can manage to collect the required blood specimens, the comparison between the risk of “clinical sepsis” and/or “confirmed sepsis^3^” between the two trial arms will form part of our secondary analyses. Although it is unclear whether BCG scarring is a marker of immune responsiveness in general and it may be that such scarring is unrelated to protection against TB, it is being captured as a marker of “vaccine take.” We will also explore whether children with a scar are less or more prone to severe illness during infancy. The study will also examine the effect of the timing of BCG administration on infant growth.

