## Intervention and co-interventions

The study intervention is an intradermal administration to HIV-1-exposed babies of 0.05 ml Tubervac® BCG vaccine from the Serum Institute of India, the vaccine currently provided by the Ugandan vaccination programme. After randomization within 24 h of birth, infants in one trial arm will receive the vaccine immediately (BCG at birth) while infants in the other arm will receive the vaccine at 14 weeks of age (delayed BCG). Our study nurses, already experts in administering all childhood vaccines, including Tubervac®, will ensure that the vaccine is administered as scheduled.

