## Follow-up and subject retention

Follow-up visits at the study clinic are scheduled on day 7 and at weeks 2, 6, 10, 14, 15, 26, 28, 48 and 52 after birth (Figs. 2 and 3). At each of these visits, data is collected on the primary and secondary study outcomes, adverse events (localized abscess formation, suppurative lymphadenitis and disseminated BCG infection), anthropometry and on potential confounding variables (see above). Mothers are given a cell phone to facilitate contact with study staff in case of an illness or other important child events.

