Also, autoregressive correlation approaches will be used to account for multiple and possibly correlated observations within the same study participant. These methods take the correlation structures into account and thereby the fact that measurements taken closer in time for an individual are likely to be more correlated than two measurements taken farther apart for that same individual. Efficacy will be calculated as 100 × (1 − RR), 100 × (1 − IRR) or 100 × (1 − HR). The prevalence of BCG scarring will be compared between the two study arms using the abovementioned approaches, as appropriate. Linear regression and or *t* tests will be used to compare the TNF and IFN-γ responses between the trial arms. We will consider adjusting for potential confounders if: (1) there are baseline imbalances between trial arms, (2) the variables for which there are such baseline differences are strongly associated with the study event or (3) they cause a ≥5% difference in the effect measures when they are added to the main model. Full case analyses will be default, but appropriate imputations will be considered for missing data.

In addition to the *intention-to-treat analysis*, where outcomes will be compared according to the random allocation, *instrumental variable analyses* will be conducted in an attempt to estimate biological/causal effects of the actual receipt of the vaccine. In these analyses, random allocation will be the instrument. To enable such analyses, actual receipt as well as the age of BCG vaccination will be captured in all participants. We will also perform *per-protocol* and *as-treated* analyses.

The primary analyses will include all HIV-1-exposed infants, adjusting for any imbalance in HIV-1 status between the two trial arms, as appropriate. However, we will also perform an analysis of the large subgroup of babies who remain uninfected with HIV-1.

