## Discussion

This trial compares the effect BCG vaccination at birth with BCG vaccination at 14 weeks of age in HIV-1-exposed babies on (1) severe illness in the first 14 weeks of life, (2) TNF, IL-1β, IL-6, IL-17, IL-22 and IFN-γ in response to mycobacterial and non-mycobacterial pathogens and (3) severe illness in 14–52 weeks of life and throughout infancy.

The study circumvents the methodological challenges of earlier observational studies that reported an association between BCG vaccination and NSEs. The exclusion criteria combined with the random allocation and large sample size will substantially reduce the likelihood that children with higher morbidity end up in either group. There will be no survival bias linked to missing vaccination cards as BCG is administered before outcome measurement. This study will be further strengthened by an exploration of immunological mechanisms for the vaccine’s hypothesized NSEs. The study will explore the trained innate immunity and heterologous immunity processes that underlie the immunological responses thought to account for the NSEs of BCG.

This trial, comparing NSEs when the vaccine is given at birth and when it is delayed, could inform the development of programmatically appropriate timing of BCG vaccination for HIV-1-exposed infants. This, in turn could importantly impact morbidity and mortality among these infants, who will constitute an increasing part of sub-Saharan African child cohorts in the years to come.

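### The scar–illness analysis counts severe illness from before the scar is read, and the age-based window for BCG reactions gives the arms 52 and 38 weeks after vaccination

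*Protocol article*

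**What the plan says.** On scars, the Secondary objectives section describes scarring as a marker of vaccine take and adds: "We will also explore whether children with a scar are less or more prone to severe illness during infancy". The Secondary outcome measures section sets the scar assessment 12 weeks after vaccination. The Intervention and co-interventions section gives BCG within 24 hours of birth in one arm and at 14 weeks of age in the other. No start point other than infancy is given for the scar–illness analysis, although the protocol sets explicit start points for other secondary analyses, such as 48 hours after randomization or 14 weeks of age.

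On safety, the Secondary outcome measures section counts adverse events through week 52 of age. Visits fall on "day 7 and at weeks 2, 6, 10, 14, 15, 26, 28, 48 and 52 after birth". The Follow-up and AE reporting sections name three events of interest: abscess at the injection site, suppurative lymphadenitis and disseminated BCG disease. The Secondary analysis section analyses safety by type, frequency and severity over the trial as a whole.

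**The concern.** An exposure measured part-way through follow-up should be related only to what happens afterwards. Illness before the scar is read cannot have been prevented by whatever the scar marks. It may instead have influenced the response to the vaccine, or both may reflect the same underlying frailty. In the delayed arm some of the counted illness even precedes the injection. The protocol's Background section takes care over this kind of problem: it reports withholding a neonatal finding because sick babies may not have been vaccinated, and it cites studies linking an absent scar to higher morbidity and mortality. A whole-infancy window would leave the trial's own scar result open to the same doubt.

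For adverse events the issue is observation time. Abscess, lymphadenitis and disseminated BCG disease cannot follow the trial vaccine until it is given. A window fixed by age therefore observes the birth arm for longer after vaccination, and a crude comparison of BCG reactions would mix that extra time with any true effect of age at vaccination.

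**Working it through.** **The plan's own figure.** The protocol gives no figure for the scar or adverse-event analyses. The only calculation to reproduce is the trial size in Table 1, which supplies the risks borrowed in step 2. With 15% against 10%, two-sided 0.05 and 90% power:

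- n per arm = [1.960·√(2·0.125·0.875) + 1.282·√(0.15·0.85 + 0.10·0.90)]² / 0.05² ≈ 917.3, rounded up to 918, or 1836 in total.
- With the continuity correction, (917.3/4)·[1 + √(1 + 4/(917.3·0.05))]² ≈ 957 per arm, or 1914 in total, as stated.

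Nothing below depends on this total.

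**Step 1: share of the scar window before the reading.** Age at reading = age at BCG + 12 weeks.

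| Arm | Age at BCG | Age at reading | Share of 52 weeks before reading | Weeks left after reading |
|---|---|---|---|---|
| Birth | 0 | 12 | 12/52 = 23% | 40 |
| Delayed | 14 | 26 | 26/52 = 50% | 26 |

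In the delayed arm 14/52 = 27% of the window precedes BCG itself. If the birth-arm reading falls at the week 14 visit, its share is also 14/52 = 27%, with 38 weeks left.

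**Step 2: share of first illnesses before the reading (illustration).** Assume that the Table 1 risks to week 14 continue at a constant hazard to week 52. The protocol does not say this.

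- Weekly hazard h = −ln(1 − p)/14, giving 0.00753 for p = 0.10 (birth) and 0.01161 for p = 0.15 (delayed).
- Birth arm: (1 − e^(−12h))/(1 − e^(−52h)) = 0.0864/0.3238 = 27%.
- Delayed arm: (1 − e^(−26h))/(1 − e^(−52h)) = 0.2605/0.4532 = 57%.

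If the hazard falls with age, these shares would be larger; if it rises, smaller. The time shares in step 1 need no such assumption.

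**Step 3: time after BCG for vaccine reactions.** Birth arm 52 − 0 = 52 weeks; delayed arm 52 − 14 = 38 weeks; ratio 52/38 = 1.37.

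This is a ratio of follow-up time. To turn it into events, assume an equal constant weekly rate r after BCG in both arms. The ratio of cumulative risks is then (1 − e^(−52r))/(1 − e^(−38r)):

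| r per week (assumed) | Birth | Delayed | Ratio |
|---|---|---|---|
| 0.0005 | 2.57% | 1.88% | 1.36 |
| 0.001 | 5.07% | 3.73% | 1.36 |
| 0.005 | 22.9% | 17.3% | 1.32 |

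If most reactions occur in the first weeks after injection, both arms capture nearly all of them and the ratio moves towards 1.

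**The case against.** The best defence is that both analyses are secondary. The scar question is explicitly exploratory, and no model is fixed for it. An age-based window for adverse events is right for comparing two randomized strategies, particularly as the protocol defines an adverse event as any harm, whether or not related to BCG. Reporting by type does not rule out a second table by time since vaccination. All of this stands, and it limits the weight of the point. It does not remove it: the scar window is stated as the whole of infancy, and the listed reactions are specific to the vaccine.

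A reader might infer more than the documents support:

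- **That the as-treated and per-protocol analyses suffer immortal time bias.** The protocol says only "We will also perform *per-protocol* and *as-treated* analyses". It sets no time origin for them, and it records that "actual receipt as well as the age of BCG vaccination will be captured in all participants", so a time-varying exposure is possible. The coding can properly sit in an analysis plan that is not shown. Any figure for such a bias would rest wholly on assumed death and non-receipt rates.
- **That the Discussion is wrong to say** "There will be no survival bias linked to missing vaccination cards as BCG is administered before outcome measurement". The sentence concerns cards lost after a death, a problem that prospective recording of receipt answers. Its last clause is loose for the delayed arm, but it is not a claim about the scar or as-treated analyses.
- **That scar prevalence is compared at unequal times because no week 12 visit is listed.** The outcome is already anchored 12 weeks after vaccination in both arms. The schedule figure is not shown, and data from unscheduled visits are used.
- **That infants who die early are counted as having no scar, which would make scars look protective.** Their scar status is missing, not negative, and complete cases are the default analysis. Both scar groups therefore consist of infants who reached the reading.

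**Conclusion.** The point holds for two analyses. The scar–illness analysis, as worded, includes illness before the reading: 23% of the first year in the birth arm (27% if read at week 14) and 50% in the delayed arm. It also includes 14 weeks before BCG in the delayed arm. These shares follow directly from the stated times. The size and direction of any resulting bias cannot be derived from the protocol.

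For BCG-specific reactions, the arms have 52 and 38 weeks after vaccination. The ratio of 1.37 becomes a ratio of roughly 1.32 to 1.36 in events only under a constant rate after BCG, and the distortion is smaller if reactions cluster early. The age-based comparison of all adverse events remains valid. The randomized comparisons, including the primary intention-to-treat analysis, start at birth or randomization, as they should, and are not touched.

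**What to change.** - **Scar and illness.** Start this analysis at the scar-reading visit (a landmark analysis). Include infants alive and followed at that visit, count only severe illness after it, and stratify by arm. The cost is fewer events: 40 or 38 weeks of the year remain in the birth arm and 26 in the delayed arm. If one window for both arms is wanted, 26 weeks after the reading is the longest that follow-up to week 52 allows.
- **BCG-specific adverse events.** Keep the comparison by age to week 52. Add one of abscess, suppurative lymphadenitis and disseminated BCG disease over the 38 weeks after vaccination in each arm. This needs event onset dates, since in the birth arm the window closes at week 38, between the week 28 and week 48 visits. It is also restricted to infants who received BCG, so it supports the randomized by-age comparison and does not replace it.

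Both are changes of wording and tabulation. They need no new visits, no additional infants and no change to the sample size.

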## Intervention and co-interventions

The study intervention is an intradermal administration to HIV-1-exposed babies of 0.05 ml Tubervac® BCG vaccine from the Serum Institute of India, the vaccine currently provided by the Ugandan vaccination programme. After randomization within 24 h of birth, infants in one trial arm will receive the vaccine immediately (BCG at birth) while infants in the other arm will receive the vaccine at 14 weeks of age (delayed BCG). Our study nurses, already experts in administering all childhood vaccines, including Tubervac®, will ensure that the vaccine is administered as scheduled.

## Key outcome measures

### Primary outcome measures

Severe illness in the first 14 weeks of lifeTNF, IL-1β, IL-6 and IFN-γ in response to mycobacterial (*M. tuberculosis* and PPD) and non-mycobacterial pathogens (*E. coli, C. albicans* and *S. aureus*) at 1, 14, 15 and 28 weeks of age

### Secondary outcome measures

Severe illness from 48 h after randomization to 14 weeks of lifeSevere illness and/or diarrhea and/or pneumonia between 14 and 52 weeks and between 0 and 52 weeks of lifeAdverse events up to 52 weeks of lifeInfant deathGrowth up to 52 weeks of lifeBCG scar 12 weeks post vaccination

## Study setting

The study is being conducted in Kawaala Health Center III, Kitebi Health Center III in Kampala district and in Mukono Health Center IV, which is located in Mukono district, 27 km east of Kampala. These centers were chosen based on their proximity to laboratories essential for specimen processing and their high number of HIV-1-infected women attending their antenatal and birth clinics. These three government facilities together conduct at least 1200 deliveries per month.

## Selection of participants, inclusion and exclusion criteria

HIV-1-infected pregnant women between 28 and 40 weeks of gestation attending antenatal care (ANC) and receiving the national elimination of mother to child (eMTCT) programme’s ART for life (Option B+) strategy are approached by the study team (Fig. 1). ANC clinics in the national programme offer routine opt-out HIV counseling, testing and ART according to the national guidelines and WHO’s Option B+ recommendation. Pregnant HIV-1-infected women attending our three study clinics are informed about the BCG study, its purpose, benefits, risks and their potential eligibility. The study team will encourage the women to deliver at the health units and to follow the national guidelines in order to mitigate MTCT of HIV during pregnancy, childbirth and the breastfeeding period.

**Fig. 1 Fig1:**
[figure not shown]
Bacille Calmette-Guérin (BCG) trial participant screening, enrollment and follow-up

For the pregnant women, these guidelines include:Daily, orally administered cotrimoxazoleInitiation of triple therapy (tenofovir, lamivudine and efavirenz) starting during pregnancy and continuing for lifeAppropriately modified obstetric practicesCounselling and support for optimal infant feeding

For the HIV-1-exposed infants, these guidelines include:Nevirapine syrup for the first 6 weeks regardless of infant feeding methodDaily cotrimoxazole starting at 6 weeks of age

For the HIV-1-infected infants, these guidelines include:Initiation of ART with zidovudine, lamivudine and nevirapine or efavirenz as the preferred regimen.Daily cotrimoxazole starting at 6 weeks

### Inclusion criteria

A baby born at a participating study clinic is included if they:Have a mother with a positive HIV-1 test (ELISA or rapid test)Are receiving periexposure prophylaxis as part of the standard/national Option B+ guidelines in UgandaHave a mother who is of legal age for participation in clinical research studies in Uganda or is an emancipated minorHave a mother/caregiver who resides within the study area, is not intending to move out of the area in the next 4 months and is likely to be traceable for up to 12 monthsHave a mother/caregiver who gives informed consent to trial participationHave a mother who has received ART for at least 4 weeks

### Exclusion criteria

A newborn child is excluded if they have:Serious congenital malformation(s)Severe illness requiring hospitalizationA birth weight <2.0 kgA mother participating in another research study on the day of enrollment or a mother who will participate in another research study within the next 3 monthsA mother or other household member with symptoms and signs of TB on the day of enrollmentA severely ill mother with a condition or conditions requiring hospitalization

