#### Screening of pregnant women

All HIV-1-positive pregnant women between 28 and 40 weeks of gestation attending antenatal care at the three clinics are informed about the study. Specifically, they are informed that if they choose to participate in the study, their infants will be randomized to receive the BCG vaccine within 24 h of birth or at 14 weeks of age. Consenting women are offered a CD4 cell count, a full blood count including hemoglobin estimation and a clinical assessment for HIV-1 disease staging and investigations for opportunistic infections, including TB. Pregnant women who are eligible following the screening and who consent to participate are recruited into the study at this first meeting. During recruitment, data on baseline characteristics and other social-demographic variables is collected.

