## Ethical considerations

According to WHO guidelines, BCG vaccination is contraindicated in children with known HIV-1 infection [22, 35, 36] because of their increased risk of disseminated BCG disease. But implementation of this guideline in many LMICs, including Uganda, is challenging. According to the expanded programme of immunization, the vaccine is to be given as soon as possible after birth. Diagnosing HIV-1 infection in infants requires a PCR which is not accessible to Ugandan children at birth. Therefore, Ugandan HIV-1-exposed newborns receive BCG at birth. On the one hand, receiving the vaccine at birth could be of potential benefit through morbidity and mortality reduction in the initial weeks of life. On the other hand, recent medical literature indicates that HIV-1-exposed uninfected infants [35, 38–41], and maybe even HIV-1-unexposed infants [48], who receive BCG somewhat later may yield more vigorous immune responses than those who receive it at birth. It is conceivable that such a delay translates into better protection against TB. Delaying vaccination may also carry the advantage of increasing the likelihood that HIV-1-exposed infants may be reliably diagnosed with respect to HIV-1 infection, both for logistic reasons but also because there is a genuine risk of HIV-1 transmission via breast milk during the first months of life [75]. This trial will compare BCG take and risk of severe illness (including death) among HIV-1-exposed children receiving the vaccine shortly after birth to such a risk in infants receiving BCG at 14 weeks of age.

The main ethical concerns specific to study are:Acquisition of TB before BCG has engendered a protective immune response (delayed BCG trial arm)Severe BCG disease among HIV-1-positive infants (early BCG trial arm)Higher incidence of severe illness during the first 14 weeks of life among the children who receive delayed BCG

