To address the first concern, the study will exclude children with household members who have signs or symptoms of TB or who have a diagnosis of TB. The risk of TB infection among trial babies will, therefore, be negligible [76]. In addition, the study will continue to actively screen and refer suspected cases to the national TB clinics until the participating infants have received BCG (at 14 weeks of age). The study will support diagnosis and initiation of treatment at the TB clinics, of any of the participants’ household members with signs and symptoms of TB from randomization until 14 weeks of age. Moreover, the study team will collaborate closely with the families to identify, treat and actively follow up the babies should there be a history of exposure to active TB or should they develop any symptoms indicative of TB. Should our study show that delayed vaccination is beneficial in terms of protecting HIV-1-exposed babies against severe illness and in the long run it leads to a policy shift, with HIV-1-exposed children from households without TB being vaccinated late, our findings will inform subsequent programmes and would thereby contribute to improved infant health.

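### The ethics section says households with a TB diagnosis are excluded and infers a negligible TB risk from this, but no listed eligibility criterion mentions a diagnosis

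*Protocol article*

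**What the plan says.** Three places in the protocol article bear on this.

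- **Exclusion criteria.** A newborn is excluded if there is a "mother or other household member with symptoms and signs of TB on the day of" enrolment. This is the only TB item in the inclusion and exclusion lists, and it does not refer to a diagnosis.
- **Ethical considerations, the concern.** The first of three named ethical concerns is that an infant in the delayed arm acquires TB before BCG has had time to protect.
- **Ethical considerations, the answer.** The article responds that "the study will exclude children with household members who have signs or symptoms of TB or who have a diagnosis of TB". The next sentence reads: "The risk of TB infection among trial babies will, therefore, be negligible". Further measures follow, among them that "the study will continue to actively screen and refer suspected cases to the national TB clinics until the participating infants have received BCG".

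The intervention section sets the delay at 14 weeks of age, and the sample size section places 1100 infants in each arm.

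**The concern.** The wait of 14 weeks without BCG is the feature of the delayed arm that needs an ethical justification on TB grounds, and the article justifies it by who is kept out of the trial. If the eligibility list does not keep those households out, the conclusion about risk has lost its stated premise. The gap concerns a relevant group: a household member already known to have TB is a potential source of exposure for a newborn, and the ethics section itself treats such a diagnosis as a ground for exclusion.

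It also touches interpretation. The same section imagines a policy of later vaccination for HIV-1-exposed children from households without TB. The trial population matches that description only if the wider exclusion is the one applied.

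**Working it through.** No arithmetic applies. The check is a comparison of two rules, followed by a search for anything else in the article that would close the gap.

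**Step 1: the two rules.** The exclusion list turns on symptoms and signs, judged on the day of enrolment. The ethics section turns on signs or symptoms, or a diagnosis, and gives no day.

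**Step 2: apply each rule to the possible households.**

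| Household member | Exclusion list | Ethics section |
|---|---|---|
| Diagnosed TB, symptoms and signs on the day | Excluded | Excluded |
| Diagnosed TB, no symptoms or signs on the day | **Eligible** | **Excluded** |
| No diagnosis, symptoms and signs on the day | Excluded | Excluded |
| No diagnosis, only symptoms or only signs | Depends on how strictly the wording is read | Excluded |
| No diagnosis, no symptoms or signs | Eligible | Eligible |

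The second row is a contradiction on any reading of the symptom wording. The fourth row is not a secure one (see the objection).

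**Step 3: does another provision supply the missing exclusion?**

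- The inclusion criteria cover maternal HIV status and treatment, infant prophylaxis, residence, legal age and consent. None concerns TB.
- The section on screening of pregnant women offers "a clinical assessment for HIV-1 disease staging and investigations for opportunistic infections, including TB". This is offered to the woman herself. It does not reach other household members, and no listed criterion makes a TB diagnosis a reason to exclude.
- The screening, referral, treatment support and infant follow-up in the ethics section are presented as additions after the conclusion on risk. They operate once the infant is in the trial.

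None of these supplies the exclusion.

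**Step 4: how does the risk statement depend on it?** The sentence on negligible risk follows directly from the sentence on exclusion and is joined to it by *therefore*. It also carries a citation that is not available here, but the reasoning printed in the article runs through the exclusion.

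**Step 5: size.** The number of infants in the second row is the number enrolled times the share of households with a diagnosed member who looks well on the day. The first factor is 2200 as planned. The article gives nothing for the second, so any count would only restate an assumption. With 1:1 allocation, about half of any such infants would fall in the delayed arm.

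**The case against.** The strongest reply has four parts.

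**The wording is loose and should not be parsed as logic.** A reader might infer that a household member with a cough but no signs passes the list because it says *symptoms and signs*. The article does not support that reading firmly. It uses the two forms interchangeably: the ethics section uses *or* for the exclusion and *and* shortly afterwards for the household members whose diagnosis will be supported. The follow-up section tells caregivers about symptoms and signs of severe illness, then asks them to make contact for any one of them. This part of the reply stands, and the point here does not rest on the conjunction. It does not answer the missing diagnosis.

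**TB in the infants would be seen anyway.** A reader might infer that the trial can detect harm only from the vaccine, because the follow-up section names "adverse events (localized abscess formation, suppurative lymphadenitis and disseminated BCG infection") and all three are BCG complications. That inference fails. The safety sections define an adverse event without regard to its relation to BCG, offer the three complications as examples, and require every adverse event to be recorded. Adverse events up to 52 weeks are a secondary outcome, and the ethics section undertakes to identify, treat and follow up babies with TB exposure or suggestive symptoms. There is no capture gap to report.

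**Other safeguards reduce the risk.** They do, and a household with an active, visible case is excluded under either rule. What remains is that these safeguards mitigate exposure after enrolment; they are not the premise given for the conclusion.

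**A journal article condenses a fuller protocol.** This would excuse an omission. Here the same article states two different exclusions, which condensing does not explain away. The reply does limit what can be said about practice: the eligibility form, the operating procedures and the screening figure are not shown.

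**Conclusion.** The point holds as an internal contradiction on a safety-related eligibility criterion. The ethics section claims an exclusion for a household TB diagnosis that the eligibility lists do not contain, and bases its statement of negligible TB risk on that claim. Applied as written, the list leaves eligible a household whose diagnosed member shows no symptoms or signs on the day.

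This rests on the article's text alone. Its size is unknown, and it has no bearing on the sample size, power or significance level. Two further inferences should be resisted. A reader might conclude that sites have been enrolling such infants, or that ethics committees were told something untrue; the article shows neither what sites work from nor what was submitted. A reader might also conclude that TB risk in the delayed arm is in fact material; the article has no figure from which to judge that. What can be said is that, if the listed criterion is the operative one, the negligible-risk statement lacks the basis given for it.

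**What to change.** - Reconcile the exclusion criteria with the ethical considerations section so that both state the same TB exclusion. The agreed text should say whether a household TB diagnosis excludes and, if so, whether only a current diagnosis or also a past one counts. It should use a single form of the signs and symptoms wording and state the day or period to which it applies.
- Check that the eligibility form carries that same text. Recruitment has been open since July 2016, so the check should come first. If the form has to change, the route is the one the article already gives for changes to eligibility criteria.
- If the narrower listed criterion is the one in use and is kept, revise the statement of negligible risk so that it rests on measures the trial actually applies.

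The cost is a sentence in each section and a check of one form. If the reconciled criterion is wider than the listed one, a few more mother-infant pairs may be excluded at screening. The analysis plan does not change.
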